##### Data Analysis—Objective 1: Scale Validation

To evaluate dimensionality, we will conduct EFA and CFA separately for cervical cancer knowledge, HPV testing knowledge, and HPV testing and self-sampling attitudes and beliefs items. The final data set will be split randomly into 2 equal samples, and one sample will be used to conduct EFA and the other sample will be used to validate the factor structure using CFA. To select the optimal number of factors, we will use the parallel analysis approach and the syntax developed by O’Connor [85]. For items within each factor, we will use item response theory modeling; for binary data (knowledge items), we will use the 2-parameter logistic regression model that accounts for item difficulty and discriminant capacity; and for ordinal data (attitudes and beliefs items), we will use the graded response model that accounts for discriminant capacity and probability of selecting a certain Likert scale score (eg, strongly agree). Concurrently, we will examine how well each item measures the latent trait by plotting the item information against the latent construct ability. We aim to retain items that cover a wide range of difficulty and have high discriminant capacity and information value. To estimate the CFA model fit, we will use the fit indices and cutoff criteria recommended by Hooper et al [86]: (1) relative (normed) chi-square test (*χ*^2^/_df_=2 to 5) by Wheaton et al [87], (2) standardized root mean square residual (<0.8), (3) root mean square error approximation (<0.06), (4) comparative fit index (≥0.95), and (5) Tucker-Lewis index (≥0.95). To evaluate internal consistency for items loading onto each factor, Cronbach *α* will be calculated.

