### Results

#### Overview

In total, 83.49% (1027/1230) valid responses were retained for analysis following data cleaning. Data analysis is ongoing. Results of study 1, including findings from the BWS analyses and the development of cervical cancer knowledge, HPV testing knowledge, HPV testing attitudes and beliefs, and HPV self-sampling attitudes and beliefs scales are expected to be published in the summer and fall of 2022.

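### The SRMR cutoff of 0.8 for CFA fit cannot reject any realistic factor structure, and the relative chi-square rule of 2 to 5 is ambiguous

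*Protocol article*

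**What the plan says.** The plan is in Study 1, Phase 1C, under Data Analysis—Objective 1: Scale Validation. Of the two random halves of the cleaned data, "one sample will be used to conduct EFA and the other sample will be used to validate the factor structure using CFA". The acceptance rules are introduced with "To estimate the CFA model fit, we will use the fit indices and cutoff criteria recommended by" a cited source, and five follow:

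- relative chi-square (chi-square/df), given as 2 to 5 and credited to a second source;
- SRMR and RMSEA: "2) standardized root mean square residual (<0.8), (3) root mean square error approximation (<0.06";
- CFI and TLI: "4) comparative fit index (≥0.95), and (5) Tucker-Lewis index (≥0.95".

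No other section gives a different SRMR value, says whether 2 to 5 is a window or a choice of ceilings, or says how many of the five must be met.

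**The concern.** SRMR is an average residual on the correlation scale. Correlations among questionnaire items rarely approach 0.8, so residuals of that size hardly occur whatever model is fitted. A limit of 0.8 therefore looks as if it can reject nothing.

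The relative chi-square rule raises a different question. A correctly specified model has expected chi-square/df of about 1, which lies below the stated range, so it matters whether the lower figure is meant as a floor.

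The CFA half is the only held-out check of the factor structures, and scale validity is the first objective of study 1. The items that survive the psychometric work go into study 2, where the scale scores serve as group comparisons and predictors. A fit criterion that cannot fail makes that check look stronger than it is.

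**Working it through.** **Inputs from the article.** SRMR <0.8; chi-square/df 2 to 5; RMSEA <0.06; CFI and TLI ≥0.95. Item counts before reduction are 14, 14, 44 and 13 (Item Selection). Expected communality is 0.2 to 0.4 (Phase 1C, Sample Size). "In total, 83.49% (1027/1230) valid responses were retained for analysis following data cleaning", and two equal halves give 1027/2, about 513 for the CFA.

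**The plan's own figure.** The thresholds are stated, not derived, so there is nothing to reproduce for them. The one calculated figure tied to this analysis, the study 1 sample size, does reproduce: (2 × 500)/0.82 = 1219.5, rounded up to 1220. It is not in dispute.

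**Step 1: SRMR of a model with no factors.** Set every model-implied correlation to zero. With p items and common correlation r, SRMR = r × sqrt((p − 1)/(p + 1)).

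- p = 14: the multiplier is sqrt(13/15) = 0.931. SRMR is 0.28 at r = 0.3, 0.47 at r = 0.5 and 0.74 at r = 0.8.
- p = 13: sqrt(12/14) = 0.926, giving 0.74 at r = 0.8.
- p = 44: sqrt(43/45) = 0.978, giving 0.78 at r = 0.8.

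For 14 items the no-factor model fails only if r exceeds 0.8/0.931 = 0.86. With equal loadings on one factor, r equals the communality, so the plan's 0.2 to 0.4 gives 0.19 to 0.37. For 13 items in three factors (4, 4 and 5 items; assumed factor correlation 0 to 0.5) the range is 0.10 to 0.25. If SRMR is averaged over off-diagonal elements only, these become 0.20 to 0.40 and 0.11 to 0.27. A model that explains nothing passes by a wide margin.

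**Step 2: does 0.08 discriminate?** The article does not give 0.08; it is taken here as the conventional value and tested by simulation. Assumptions: N = 513, 13 normal items, communality 0.3 or 0.6, a one-factor maximum-likelihood fit, 60 replicates per scenario.

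| True structure | Mean SRMR | Pass <0.8 | Pass <0.08 |
|---|---|---|---|
| One factor (fit is correct) | 0.015 to 0.026 | 100% | 100% |
| Three factors, correlation 0 or 0.3 (fit is wrong) | 0.09 to 0.22 | 100% | 0 to 3% |

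**Step 3: chi-square/df read as a window.** For a correct model, chi-square/df has expectation 1. From the central chi-square distribution, the probability of a value below 2 is 0.925 at 5 df, 0.995 at 20 df and 0.999997 at 65 df (one factor, 13 items: 78 − 13 = 65). In the simulation none of the 120 correct fits fell between 2 and 5; their mean was 1.03 to 1.05. A literal window would exclude almost all of them.

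**Step 4: chi-square/df read as a range of ceilings.** Good models then pass, but a model at, say, 3.5 passes under a ceiling of 5 and fails under a ceiling of 2. The text does not settle which applies.

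**Step 5: the other three indices.** In the wrong-structure scenarios mean RMSEA was 0.10 to 0.23, mean CFI 0.42 to 0.60 and mean TLI 0.30 to 0.52. All are far outside the plan's limits.

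**The case against.** The best defence is that little depends on these two figures. RMSEA, CFI and TLI are strict as printed and rejected the wrong structures in the simulation. If all five criteria must hold, the loose SRMR limit alone would not let a bad structure through. Item selection also rests on item response theory, the number of factors on parallel analysis, and internal consistency on Cronbach alpha. A dropped zero in a condensed article is the obvious explanation for 0.8. All of this stands and limits the weight of the point; it does not make 0.8 a working cutoff.

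A reader might infer that the chi-square rule definitely rejects better-fitting models. The article does not support that: it never says values below 2 fail, and a strict and a lenient upper limit is a plausible meaning.

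A reader might also infer that the rule contradicts RMSEA <0.06. With an unscaled chi-square and N = 513, that limit corresponds to chi-square/df below 0.06² × 512 + 1 = 2.84, so values from 2.84 to 5 meet one rule and miss the other. One index being stricter than another is normal in a set of five and is not a contradiction. The 2.84 also assumes an unscaled statistic, while the items are binary or 7-point ordinal and the article names no CFA estimator.

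**Conclusion.** The SRMR cutoff is wrong as written. At 0.8 it accepts a no-factor model at any plausible inter-item correlation, so it contributes nothing to the validation. This follows from algebra and the plan's own communality range. That the intended value was 0.08 is an inference, supported by the simulation under its assumptions of normal items and equal loadings.

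The chi-square criterion is ambiguous rather than shown to be wrong: one reading excludes nearly all correct models, the other leaves the ceiling undefined.

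The overall effect is modest. It would be going too far to conclude that the scales will be accepted without a real test of fit, since three demanding indices remain. How much they protect depends on how many criteria must be met, which the article does not say.

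**What to change.** - State the SRMR cutoff as <0.08, after checking it against the source that the article cites.
- State relative chi-square as a single upper bound with no lower limit, or label it descriptive. Do not derive the bound from RMSEA <0.06: at a given N, and with an unscaled chi-square, RMSEA is a function of chi-square/df alone, so the two rules would become the same test.
- Apply the corrected rules before the study 2 item set is fixed.

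The cost is two edited figures. As of May 2022 the study 1 analysis was still running and study 2 data collection had not begun. Any CFA already fitted needs only its SRMR and chi-square/df read again against the corrected limits.

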###### BWS Preferences

To analyze BWS preference data, we will use the counting and modeling approaches described by Aizaki and Fogarty [64]. Consistent with the counting approach, for domain A (screening interval) and domain B (age of initiation), we will calculate the best-minus-worst score (higher scores reflect higher preferences) for each attribute (eg, HPV test) and attribute level (eg, 3 years [for screening interval] and 25 years [for age of initiation]). For the modeling approach, we will use conditional logistic regression to model preferences as a function of the sum of the values of attributes and attribute levels [64]. For attributes and attribute levels, we will estimate odds ratios and 95% CIs.

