##### BWS for Screening Preferences

Following the orthogonal main effects design recommended by Aizaki and Fogarty [64] and using the R software packages, *DoE.base* [82] and *support.BWS2* [64], a full set of questions was developed for each of our 2 domains: screening intervals (domain A) and age of screening initiation (domain B). To examine preferences in domains with 4 attributes (ie, screening methods), each of which have 3 attribute levels (ie, screening interval options [domain A] and screening initiation options [domain B]), participants must answer 9 questions that contain the same number of randomly assigned combinations of attribute levels (corresponding to the defined attributes). Therefore, participants answered 18 items; 9 related to cervical cancer screening intervals and 9 related to age of initial screening. Items within each domain were presented randomly for each participant.

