#### Data Analysis

Corresponding to objective 1, we will conduct univariate analyses (means and proportions) for scale items (eg, knowledge and attitudes) and bivariate analyses (2-tailed *t* tests and chi-square tests) to estimate the differences between adequately screened women and underscreened women. We will calculate the effect size using Cohen *h* and Cohen *d* for proportions and continuous variables, respectively. Corresponding to objective 2, we will estimate the associations between psychosocial factors and intentions of HPV testing and self-sampling using multinomial logistic regression and model the log odds of PAPM stages (dependent variable) as a linear combination of the independent variables (eg, HPV testing knowledge and BWS preference scores). We will report odds ratios and 95% CIs of being in a PAPM stage versus the reference category (ie, unengaged) for each independent variable. Initially, we will conduct bivariate analyses to estimate the association between the outcome and independent variables. Then, independent variables showing significant associations (*P*<.10) will be entered simultaneously in the final model. We selected the following indices to report model fit: (1) Cox-Snell *R*^2^, (2) Cragg-Uhler *R*^2^, and (3) McFadden *R*^2^ [39,92]. We will use the Hausman-McFadden test to evaluate the final model for independence of irrelevant alternatives, which postulates that a person’s choice (ie, PAPM stage) is unchanged by other available choices (ie, fewer PAPM stages) [93]. Analyses will be conducted separately for underscreened women and adequately screened women. Analyses will be conducted using SPSS (IBM Corporation), R software (R Foundation for Statistical Computing), and STATA (StataCorp).

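### The best-worst scaling model names no allowance for each woman's nine repeated choices, so default 95% CIs for test-type odds ratios would be too narrow if preferences differ between women

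*Protocol article*

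**What the plan says.** Under Study 1, Phase 1C, the section BWS for Screening Preferences describes "domains with 4 attributes (ie, screening methods), each of which have 3 attribute levels". On the number of questions it says that "participants answered 18 items; 9 related to cervical cancer screening intervals and 9 related to age of initial screening".

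The BWS Preferences section plans two analyses. In the counting analysis, "we will calculate the best-minus-worst score (higher scores reflect higher preferences) for each attribute" and each attribute level. For the second it says "For the modeling approach, we will use conditional logistic regression to model preferences as a function of the sum of the values", meaning those placed on the tests and on their levels. It cites a methods paper and adds: "For attributes and attribute levels, we will estimate odds ratios and 95% CIs". It does not say how the standard errors will be obtained, and it mentions no respondent-level term, clustering or resampling.

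The number of women is in the Study 1 Results: "In total, 83.49% (1027/1230) valid responses were retained for analysis following data cleaning".

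The Study 2 Data Analysis section lists candidate predictors of intention stage as ("eg, HPV testing knowledge and BWS preference scores"). Those with P<.10 in bivariate analysis then enter the final multinomial model together.

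**The concern.** A woman who favours self-sampling tends to favour it in all nine questions of a domain. Conditional logistic regression removes what is common to a question, but not what is common to a woman. Its default variance counts every answered question as a separate unit of information. If women differ in their preferences, the test-type estimates carry between-woman variation that this variance leaves out.

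The preference results are meant to be used. The Discussion says that women's preferences will be set against proposed guidelines and will inform screening recommendations. An interval that is too short could present a weak average preference for one test over another as established.

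A second dependence arises if best-minus-worst scores become predictors in Study 2. Each question gives one item +1 and another −1, so a woman's scores within a domain are linearly tied.

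**Working it through.** **Inputs from the protocol.** 4 attributes with 3 levels each and 9 questions per domain (BWS for Screening Preferences); 1027 women (Study 1 Results); conditional logit with 95% CIs (BWS Preferences).

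**The plan's own figure.** The full factorial has 3^4 = 81 profiles. The smallest orthogonal main-effects array for it has 9 runs, with every pair of columns balanced. That gives 9 questions per domain and 2 × 9 = 18 in all, as stated.

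**Units of information.** 1027 × 9 = 9243 choices per domain, from 1027 independent women.

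**Generic guide.** With nine equally correlated contributions per woman, the SE inflation is sqrt(1 + 8ρ): 1.04 at ρ = 0.01, 1.18 at 0.05, 1.61 at 0.2 and 2.24 at 0.5. The protocol gives no ρ.

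**Simulation of this design.** 9-run array, 12 possible best-worst pairs per question, 11-parameter conditional logit, N = 1027. The coefficients and between-woman SDs are assumptions. When the utilities of the four tests vary between women and the level effects do not, the test-type odds ratios behave as follows:

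| Between-woman SD (log-odds) | True SE / model SE | Coverage of default 95% CI |
|---|---|---|
| 0.25 | 1.13 | 92% |
| 0.5 | 1.44 | 82% |
| 0.75 | 1.66 | 75% |
| 1.0 | 1.81 | 74% |
| 1.5 | 2.24 | 65% |

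Respondent-clustered SEs covered 94% to 96% in these settings. With no heterogeneity, the clustered and model SEs agree (ratio 1.00).

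**Sensitivity to how women differ.**
- Reference test held fixed, only the other three vary: test-type ratio 1.06 at SD 0.25, 1.22 at 0.5 and about 1.52 at 1.0. These are smaller because each contrast with the reference then varies less.
- Level effects vary with the same SD as test type (0.5 to 1.5): test-type ratio 1.28 to 1.62, levels 1.05 to 1.12.
- Only test type varies (SD 0.5 to 1.5): level ratio 0.94 down to 0.74, so default CIs for levels are too wide. A level effect is compared within the same woman across questions, and a stable test preference makes her answers less variable than the model supposes.

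**Absolute size.** The model SE for a test-type log odds ratio is about 0.018, so the half-width is 1.96 × 0.018 = 0.035 and exp(0.035) ≈ 1.04. At SD 1.0 the clustered SE is about 0.034, so the half-width is 1.96 × 0.034 = 0.067 and exp(0.067) ≈ 1.07. Only estimated odds ratios between about 1.04 and 1.07, or their reciprocals, would change verdict. At SD 1.5 the upper figure is exp(1.96 × 2.24 × 0.018) ≈ 1.08.

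**Study 2 scores.** Each question contributes +1 − 1 = 0, so the 12 level scores of a domain sum to zero for every woman, as do the 4 test scores. Their ranks are 11 and 3. A complete set entered with an intercept and no reference left out is therefore collinear by one for every domain.

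**The case against.** The strongest reply is that the protocol does not say the choices are independent. Conditional logistic regression fixes the choice model, not the variance estimator. Clustered SEs would satisfy every word of the section, and a condensed article may leave that option to a fuller plan or to the methods paper it cites. This stands against any claim that the plan is committed to independence. It does not remove the point: the section states the data structure, the model and the interval, and the model fitted as named, with its default CIs, mis-sizes those intervals whenever women's preferences differ.

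The reply on size also largely stands. A reader might infer that all the BWS intervals will be far too narrow. The protocol contains no heterogeneity figure, and for interval and age levels, which the Introduction treats as the main points of contention, the error is small or runs the other way. The absolute shift is small even for test type. The model is described under preparatory Study 1, and a counting analysis is reported beside it.

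On Study 2, a reader might infer that the regression is not identified as planned. The text names BWS scores only as an example of a predictor. The Study 2 Sample Size section allows 15 predictors, which cannot hold the 2 × 12 = 24 level scores of both domains. Nothing shows that a complete set will be entered, although the P<.10 rule does not prevent it for a smaller set such as the four test scores.

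**Conclusion.** The point holds conditionally. If the default CIs of the named model are used, and if women differ in how they value the tests, the test-type intervals are too short: the SE is understated about 1.1- to 2.2-fold for assumed SDs of 0.25 to 1.5 log-odds when only test-type utilities vary, and less when level preferences vary as well. Interval and age intervals may be slightly short or too long. Both conditions and every SD are assumptions. The practical effect is confined to odds ratios within a few percent of 1.

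The documents do not support saying that the plan treats the choices as independent, or that all the BWS intervals will be far too narrow. The sum-to-zero constraint on the scores is exact algebra, but it causes trouble in Study 2 only if a full set of scores is entered together. The change is worth making because it costs almost nothing and corrects the intervals in either direction.

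**What to change.** Keep the conditional logit and add one sentence: the 95% CIs for BWS odds ratios use a sandwich variance clustered on respondent. With 1027 clusters this is reliable, and it leaves the odds ratios themselves unchanged. A bootstrap that resamples women would serve as well. A mixed logit with respondent random effects is also acceptable, but its odds ratios are conditional on the woman and should be labelled so.

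For Study 2, state that if a full set of best-minus-worst scores from a domain passes the P<.10 screen, one reference score per domain is left out, or prespecified contrasts are used (for example self-sampling minus Pap), and that odds ratios are read against that reference.

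The cost is one fitting option and two sentences, with no new data. Test-type CIs become wider if preferences differ; level CIs may move either way.

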### Results

#### Overview

In total, 83.49% (1027/1230) valid responses were retained for analysis following data cleaning. Data analysis is ongoing. Results of study 1, including findings from the BWS analyses and the development of cervical cancer knowledge, HPV testing knowledge, HPV testing attitudes and beliefs, and HPV self-sampling attitudes and beliefs scales are expected to be published in the summer and fall of 2022.

#### Objective 2: Questionnaire Feasibility

Preliminary results suggest high level of feasibility. Through the recruitment methods of Dynata, data collection was completed within 2 weeks. As detailed in the *Data Cleaning* section, overall, data were of good quality, with the exclusion of 16.5% (203/1230) of complete responses owing to poor quality, being consistent with previous research in our laboratory and expectations for survey research [39,84,88]. The mean response time (after data cleaning) was 30.4 (SD 20.5) minutes, consistent with other surveys conducted by our research team [89]. It is possible that some participants left the survey and returned to it later, which could explain the slightly higher response time than our estimated 25 minutes. Given that the scales in study 2 will be made more concise through psychometric analyses applied to responses from this study, we expect the survey in study 2 to be shorter in length. Of the 1392 participants who were eligible and began the survey, 1230 (88.36%) participants completed the survey, with an attrition rate of 11.64% (162/1392) (refer to Figure 4 for a diagram detailing participant attrition). Attrition primarily occurred in the HPV attitudes and beliefs section (50/162, 30.86%), which is the longest section of the survey, with 44 items. We expect that the validation and shortening of this scale for study 2 will help to address this issue.

**Figure 4 figure4:**
[figure not shown]
Study 1—participant flow diagram. BWS: best-worst scaling; HPV: human papillomavirus.

## Study 2: Expanded Population-Based Survey of Canadian Women

### Methods

#### Study 2: Ethics Approval

Study 2 received approval from the research ethics board of the Centre intégré universitaire de santé et de services sociaux West-Central Montreal (project ID 2022-2960) in July 2021. Informed consent will follow the same procedure as that in study 1.

